### Data auditing

Prior to performing the final study analyses, data will be checked by the statistician who will be assisted by research assistants in this process. These individuals will be blinded to the group assignment of the participants.

### Sample size estimates

A study investigating the effects of aerobic exercise on inflammation reduction [24] demonstrated effect sizes (Cohen’s *d*) varying between .40 and .77 for IL-6 and IL-10 and their ratio, which would be considered a medium to large effect. Few studies have investigated the effect of prebiotic supplements on inflammation, though similar magnitude effect sizes were reported for a prebiotic supplement intervention on changes in free circulating uremic solutes indoxyl sulfate and p-cresol sulfate, key indicators of adverse outcomes of CKD [9], though those changes were not found to be significant in that small sample study. Based on these studies, we anticipate medium effect sizes, and with power set at .80, and alpha set at .05, a sample size of 60 (15 per group) is predicted to be sufficient for detecting significant two-way interactions specified in the statistical analysis section. To account for any dropouts from the protocol, missing data will be addressed through multiple imputation, and results of all analyses averaged over multiple imputed datasets. All variables in the analysis will be examined for assumptions for all statistical tests. Data will also be examined in a per-protocol analysis, using only data from participants in all groups who completed 70% or more of their assigned exercise sessions and/or supplement use and who provided outcome data on the relevant variables.

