All other aspects of the protocol remain in place. There are no plans to resume the exercise components of this particular study. Additional modification will be needed for the statistical analyses. Given the reduced number of participants completing the exercise portion of the protocol, the intended comparison between the prebiotic and exercise conditions will only be exploratory in nature. The effect of the prebiotic compared to placebo will be examined by a 2 (prebiotic vs. placebo) × 3 (time) mixed factor ANOVA.

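### The claim that 60 patients give 80% power for a medium effect is not supported by the Cohen's d values it cites, unless repeated measurements correlate at about 0.75 to 0.8 or more

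*Protocol article*

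**What the plan says.** The Sample size estimates section of the protocol article rests on two sources. An exercise study gave Cohen's d "varying between .40 and .77 for IL-6 and IL-10 and their ratio". For the supplement, "similar magnitude effect sizes were reported for a prebiotic supplement intervention on changes in free circulating uremic solutes"; the section adds that those changes were not significant in a small sample. From these it expects an effect of medium size, takes .80 for power and .05 for alpha, and concludes: "a sample size of 60 (15 per group) is predicted to be sufficient for detecting significant two-way interactions specified in the statistical analysis section".

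The Statistical analyses section defines the two-way interactions as supplement by time and exercise by time within a 2 × 2 × 3 mixed ANOVA. With 15 per group, each sets 30 patients against 30. The same section names IL-6 and IL-10 as the variables of main interest.

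On losses, the article says: "To account for any dropouts from the protocol, missing data will be addressed through multiple imputation". It gives no expected rate and no inflation of the sample.

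The Update section removes exercise, replaces the main analysis with a 2 (prebiotic or placebo) × 3 (time) mixed ANOVA, and says "All other aspects of the protocol remain in place". It gives no new power statement.

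**The concern.** Cohen's d is the only effect metric in the section, and the planning effect is said to follow from the cited studies. In that metric a medium effect is conventionally 0.5, which lies inside the cited range. A 30 versus 30 comparison looks too small to detect d = 0.5 with 80% power unless the repeated measurements are strongly correlated.

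What is at stake is how a null result is read. If 80% power is taken at face value, a non-significant supplement by time interaction will look like evidence against a medium effect. Under moderate correlation the trial would have had roughly even odds, or worse, of detecting one. The trial now being run tests only the supplement, whereas the effect size for inflammation comes from an exercise study.

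**Working it through.** **Inputs from the article.** N = 60, 15 per group, so 30 v 30 per two-way interaction; power .80; alpha .05; cited d from .40 to .77; three time points.

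**Assumptions, not in the article.** Medium means d = 0.5 or, by the ANOVA convention, f = 0.25. The t test is two-sided. The within-person correlation ρ is the same between all pairs of visits and is varied. Dropout is 20% where used. The 30 v 30 split is carried over to the 2 × 3 design.

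**1. Can the plan's figure of 60 be reached?** The usual repeated-measures interaction formula is λ = f²·N·m/(1 − ρ), with m = 3. For f = 0.25 and N = 60, λ = 0.0625 × 60 × 3/(1 − ρ) = 11.25/(1 − ρ).
- Two groups, 2-df test: power is 0.85 at ρ = 0, 0.95 at ρ = 0.3 and 0.99 at ρ = 0.5. The smallest N for 80% is 54, 38 and 28, so 60 is sufficient.
- Four groups, 6-df test: the smallest balanced N is exactly 60 at ρ = 0.25. This is an omnibus group by time test, not the 2-df two-way interaction that the section says is powered.

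**2. What f = 0.25 means in units of d.** Let d be the between-group difference in change by week 16, in baseline SDs.
- Effect builds linearly (0, ½, 1): f = d/√24, so f = 0.25 means d = 0.25 × 4.899 = 1.22.
- Full effect by week 8 (0, 1, 1): f = d/√18, so f = 0.25 means d = 0.25 × 4.243 = 1.06.

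Both exceed the largest cited d of .77. In the other direction, d = 0.5 is f = 0.10 (linear) or 0.12 (full by week 8), not 0.25.

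**3. d as a standardised difference in change.** Noncentral t, 58 df, noncentrality d·√(30/2).

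| d | noncentrality | power |
|---|---|---|
| 0.40 | 1.55 | 0.33 |
| 0.50 | 1.94 | 0.48 |
| 0.77 | 2.98 | 0.84 |

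For d = 0.5, 80% power needs 64 per arm, 128 in all. The smallest d with 80% power at 30 v 30 is 0.74.

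**4. d in baseline SDs, 2-df interaction F test, N = 60.** λ = f²·60·3/(1 − ρ). For d = 0.5 and ρ = 0.5 this is (0.25/24) × 180/0.5 = 3.75 (linear) or (0.25/18) × 180/0.5 = 5.00 (full by week 8).

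| d | ρ | power, linear | power, full by week 8 |
|---|---|---|---|
| 0.50 | 0.3 | 0.28 | 0.37 |
| 0.50 | 0.5 | 0.38 | 0.49 |
| 0.50 | 0.7 | 0.59 | 0.72 |
| 0.50 | 0.8 | 0.78 | 0.89 |
| 0.40 | 0.5 | 0.26 | 0.33 |
| 0.77 | 0.5 | 0.75 | 0.87 |

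For d = 0.5, power first reaches 0.80 at ρ of about 0.75 (full by week 8) or 0.815 (linear).

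**5. With 20% lost (24 v 24).** For d = 0.5 the F test at ρ = 0.5 has power 0.31 (λ = 3.0) to 0.40 (λ = 4.0), and the t test on change has 0.40. The smallest d with 80% power on change is 0.83.

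**The case against.** The strongest reply is that the article claims only that 60 is sufficient, and under a standard convention it is. With f = 0.25 the 2-df interaction has power of at least 0.85 at 60, and still 0.76 at ρ = 0 and 0.97 at ρ = 0.5 with 48 patients. A reader might infer that the figure cannot be reproduced at all, or that smaller required numbers such as 28 or 40 count against it. Neither follows: a smaller requirement supports sufficiency, and one four-group setting returns exactly 60. What this route cannot do is connect to the evidence given for it, because it needs an effect of 1.06 to 1.22 SD.

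A reader might also infer that power simply is 40 to 50%. The article does not support that either. It gives no number for medium, does not say what kind of d it cites, and states no correlation. At d = 0.5, power is 0.59 to 0.72 for ρ = 0.7 and passes 0.80 near 0.75 to 0.8. At d = 0.77, it is 0.75 to 0.87 even at ρ = 0.5.

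A third tempting reading is that the article claims imputation restores power. It says only that missing data will be handled that way. The narrower point stands: no allowance for loss is shown, and imputation does not recover the information lost with patients who drop out.

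It is also fair that a journal article may leave the formula, software and correlation to a fuller document, so their absence alone is no fault. The Update does acknowledge that the analyses need modification, and the article cites a prebiotic study alongside the exercise one. That study concerns uremic solutes, however, not IL-6 or IL-10, and the power claim itself was left as it was.

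**Conclusion.** The concern holds in conditional form. In the metric the article cites, 80% power for a medium effect with 60 patients is not supported at ordinary within-person correlations. At d = 0.5, power is 0.48 on standardised change, or 0.38 to 0.49 by the interaction F test at ρ = 0.5; with an assumed 20% loss the F-test figures fall to 0.31 to 0.40. The claim becomes true with ρ of about 0.75 to 0.8 or more, with an effect near the top of the cited range on the change scale, or with f = 0.25. If f = 0.25 was the route taken, which the article does not say, the fault is a mismatch between d and f.

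These figures rest on d = 0.5, equal correlations between visits, two linear-or-plateau effect patterns, a 30 v 30 split and the assumed dropout. None of them except the split follows from the article, and the split itself is carried over from the four-group plan to the 2 × 3 design, for which no power is stated.

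**What to change.** Replace the power sentence with one for prebiotic versus placebo in the 2 × 3 design. Give the effect in a single metric, say whether it is scaled by the SD of change or of baseline, and state the assumed within-person correlation and dropout. For example: *With 30 v 30 evaluable, there is 80% power at two-sided alpha .05 for a standardised difference in change of about 0.74 (0.83 at 24 v 24), and power of about 0.48 for d = 0.5.* If f = 0.25 was used, say so and give the difference in change it implies. Keep multiple imputation as the method for missing data, but state the dropout allowance separately.

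The cost is rewording and a less favourable stated power. No increase in enrolment and no change to the analysis is needed.

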### Dissemination policy

Upon the completion of data collection, the PI and the research team will endeavor to publish the findings of this trial in peer-reviewed journals whatever the outcome of the trial. The PI will also submit the findings to be presented at relevant professional meetings.

## Discussion

The purpose of the study is to examine the effect that 16 weeks of supplementation with the prebiotic, RS-2, has on the composition of the microbiota of a sample of stage 3–4 CKD patients. In addition, we will be monitoring the impact of this prebiotic on the levels of key uremic toxins (PCS & IS), markers of inflammation (CRP, TNF-a, IL6,IL10, MCP1), oxidative stress (MDA and 8-isoprostanes F2a,) and some cardiovascular parameters (arterial stiffness and blood pressure) that are known to impact upon the development of CVD. The potential additive effect of 16 weeks of moderate intensity aerobic exercise on the aforementioned variables will also be explored. Since many of the previous studies performed with RS-2 supplementation have been completed with ESRD patients, this study is one of the first to examine the impact of this supplement on the most prevalent stages of kidney disease, stage 3 & 4 [1].

The success of this protocol depends upon the adherence to two behavioral interventions, namely nutritional supplementation with RS-2 and aerobic exercise training for those randomized to the exercise groups. To enhance compliance to the nutritional aspects of the study, all participants have individual counseling sessions with the study dietitian to review various strategies to consume the product. At two-week intervals during the study, a research assistant is tasked with attempting to contact the participants to determine if there are any concerns with taking the supplement. If there are any such issues, the registered dietitian is informed and the issue is addressed with the participant as soon as it is feasible.

The inclusion of supervised exercise training is a strength of the study [25]. There is some evidence that exercise training alone has a favorable effect on the composition and function of the microbiota in some individuals [26, 27]. This information has not been previously examined in persons with CKD who are known to have a dysfunctional microbiota [28, 29]. Having participants directly supervised during each training session ensures that participants are given the guidance that they need to successfully complete their prescribed exercise training [25]. This also builds in a sense of accountability.

### Update

Due to the ongoing COVID-19 pandemic, we have been forced to make some changes to our original protocol. All of these changes have been reviewed and approved by the IRB of the College in addition to the department that oversees the grant. All recruitment is now being done remotely. Patients are being screened by the study recruiter (EE) who then gets permission from prospective participants for the PI to call to give details about the study. Once a participant agrees to enroll in the study they are sent the consent form and a COVID-19 waiver either electronically or in the mail. The participant must sign each of these prior to starting the study. The day prior to each research session, the PI calls the participant to complete a COVID-19 symptom screen which consists of a series of seven questions and confirm the details for the upcoming visit including the necessity of the participant to wear a mask. On the day of the visit, the PI, wearing full personal protective equipment, meets the participant outside of the building and takes a temperature reading before the participant enters the building. Following this, the PI continues to complete the study protocol as previously described.

The major change to the entire protocol is the removal of the exercise component. Participants no longer complete the graded exercise test nor are they assigned to any exercise intervention. This was necessary due to the shut down that occurred due to COVID 19 and due to the fact that individuals from outside of the College community are not allowed access to the training facilities where the exercise would have taken place. This was done in an effort to minimize the risk of participants or researchers contracting the COVID-19 virus.

Another adjustment that was made to the protocol was a switch to remote counseling by our dietitian. After visit 2, the participant no longer meets with the dietitian (DC) in person but rather receives dietary counseling over the phone regarding how to take the supplement.

All other aspects of the protocol remain in place. There are no plans to resume the exercise components of this particular study. Additional modification will be needed for the statistical analyses. Given the reduced number of participants completing the exercise portion of the protocol, the intended comparison between the prebiotic and exercise conditions will only be exploratory in nature. The effect of the prebiotic compared to placebo will be examined by a 2 (prebiotic vs. placebo) × 3 (time) mixed factor ANOVA.

## Data Availability

The PI will have access to the completed data set which will be used for publications purposes only. It is therefore our intent to publish our data in reputable peer-reviewed journals so that the public can have access to our findings. We can make data available to those interested upon request.

## Abbreviations

CRP: C-reactive protein
CVD: Cardiovascular disease
CKD: Chronic kidney disease
ESRD: End-stage renal disease
RS-2: High amylose maize resistant starch type 2
IL-6: Interleukin 6
IL-10: Interleukin 10
MCP1: Monocyte chemoattractant protein 1
PWV: Pulse wave velocity
TNFα: Tumor necrosis factor alpha,
SBP: Systolic blood pressure
DBP: Diastolic blood pressure
